### Comparison of the Effect of Massage and Range of Motion Exercises on Intensive Care Units Acquired Weakness

#### Protocol summary

##### Study aim

Comparison of the Effect of massage and range of motion exercises on intensive care unit acquired weakness in hospitals affiliated to Kerman University of Medical Sciences, 2019

##### Design

A clinical trial with two intervention groups with parallel groups, without a control group, without blinding, randomized

##### Settings and conduct

The study will be done as an interventional study in two groups of massage and range of motion exercises in two ICUs in two hospitals.

##### Participants/Inclusion and exclusion criteria

The study sample consists of all patients admitted to the intensive care unit with inclusion criteria. Inclusion criteria: First day ICU patients (patients undergoing invasive mechanical ventilation, non-invasive mechanical ventilation, and patients not under mechanical ventilation), FOUR Score in patients not mechanically ventilated (ER 4, MR 4, CR 4, R 4) and in patients undergoing mechanical ventilation (ER 4, MR 4, CR 4, R 1). Exclusion criteria: Having amputation, upper and lower extremity fractures, neuromuscular diseases (myasthenia gravis, Guillotine, botulism, and pesticide poisoning, etc.), deep vein thrombosis, skin diseases, metabolic disorders: hypocalcemia, hypophosphatemia, hypomagnesemia, and an allergy to olive oil in the massage group.

##### Intervention groups

Massage group: The intervention in this group begins on the first day of admission. In addition to providing routine care, the researcher massages the entire body once a day for 7 consecutive days using the Swedish massage style. Range of motion exercises group: The intervention in this group begins on the first day of admission. In addition to providing routine care, the researcher performs a passive and active range of motion exercises once a day for 7 consecutive days.

#### Main outcome variables

Change in the score of Intensive Care Units Acquired Weakness

#### General information

##### Reason for update

##### Acronym

##### IRCT registration information

IRCT registration number: **IRCT20200203046358N1**

Registration date: **2020-02-14, 1398/11/25**

Registration timing: **prospective**

Last update: **2020-02-14, 1398/11/25**

Update count: **0**

##### Registration date

2020-02-14, 1398/11/25

##### Recruitment status

**Recruitment complete**

##### Funding source

##### Expected recruitment start date

2020-02-20, 1398/12/01

##### Expected recruitment end date

2020-07-22, 1399/05/01

##### Actual recruitment start date

empty

##### Actual recruitment end date

empty

**Trial completion date**  
empty

**Scientific title**  
Comparison of the Effect of Massage and Range of Motion Exercises on Intensive Care Units Acquired Weakness

**Public title**  
Comparison of the Effect of Massage and Range of Motion Exercises on Intensive Care Units Acquired Weakness

**Purpose**  
Supportive

**Inclusion/Exclusion criteria**  
**Inclusion criteria:**  
 First day ICU patients (patients undergoing invasive mechanical ventilation, non-invasive mechanical ventilation, and patients not under mechanical ventilation) FOUR Score in patients not mechanically ventilated (eye response score 1, motor response 2, corneal reflex 2, respiration 1) and in patients undergoing mechanical ventilation (eye response score 2, motor response 2, corneal reflex 2, respiration 1)  
**Exclusion criteria:**  
 Having amputation Having upper and lower extremity fractures Having neuromuscular diseases (myasthenia gravis, guillotine, botulism, and pesticide poisoning, etc.) Having deep vein thrombosis Having skin diseases Having metabolic disorders: hypocalcemia, hypophosphatemia, hypomagnesemia Having allergy to olive oil in the massage group

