**Sample size**  
Target sample size: **10**

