**Randomization description**  
Samples will be divided into two groups (massage group, range of motion exercises) using the minimization method. In the minimization method, sex, age ( $\pm 2$ ), and hospital are considered as matched variables at baseline. In other words, in each hospital, the first sample will be placed in one of the groups using the lottery, and the next sample will be randomly assigned to one of the groups after matching the groups by gender and age. This process will continue until the sample volume is complete. Random allocation of samples to each group will be done by a researcher who has no role in intervention and outcome measurement.

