**Description**  
Change in the score of Intensive Care Units Acquired Weakness

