#### Description

Intervention group: Massage group: Intervention in this group begins on the first day of admission. In this group, in addition to providing routine care, the researcher/fellow researcher massages the entire body once a day for 7 consecutive days using the Swedish massage style. To do the massage, first placing the mat so that the patient's mattress will not get oily and the patient is positioned. Massage is in such a way that the patient will be in the supine position and the head is positioned at an angle of 30 to 45 degrees. Swedish massage comprises strokes, gliding, and vibrating. For massage, olive oil is used to the extent that facilitates massage (approx. 20 ccs). The whole-body massage will be continuous and lasts 30-60 minutes. Massage is performed at 3 to 7 pm when the intensive care unit workload is less. After the massage is completed, the patient's entire body is cleaned with a napkin to cleanse the remaining oil on the patient's body.

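### Olive-oil allergy excludes a patient only in the massage arm, so eligibility as written depends on the allocated group

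*Protocol*

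**What the plan says.** The Exclusion criteria section of the Protocol lists "Having allergy to olive oil in the massage group". The Participants section of the protocol summary has the same restriction: "an allergy to olive oil in the massage group". The other exclusions (amputation, limb fractures, neuromuscular disease, deep vein thrombosis, skin disease, metabolic disorders) apply to everyone; only this one names an arm.

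The intervention descriptions explain the restriction: olive oil, about 20 cc, is used for the massage and is not mentioned for the exercises.

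On allocation, the Randomization description says "Samples will be divided into two groups (massage group, range of motion exercises) using the minimization method", with sex, age and hospital as the factors. After the first patient in each hospital, "the next sample will be randomly assigned to one of the groups after matching the groups by gender and age". Allergy is not a factor. The Blinding section says that the trial is not blinded. The planned size is "Target sample size: 10", and the primary outcome is "Change in the score of Intensive Care Units Acquired Weakness".

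The Protocol does not say that allergy is checked in all candidates before allocation. Nor does it say what happens to an allergic patient who is allocated to massage.

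**The concern.** A candidate belongs to no group until allocated. An exclusion that holds only in one group therefore cannot be settled at screening; taken at its word, it is applied after the arm is known. The massage arm then holds only non-allergic patients, while the exercise arm may hold both kinds.

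Random allocation supports the comparison because the same eligible population feeds both arms. A criterion that removes patients from one arm only weakens that. The blinded status matters here too: because the trial is open-label, nothing hides the arm from the people applying the criterion. With so few patients planned, one patient handled in this way is a visible share of an arm.

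**Working it through.** **1. What the text permits.** The Protocol has no figure to reproduce on this point, so the first check is of the wording. Setting the criterion beside the Randomization description, an allergic candidate can be handled in three ways:

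- *Checked after allocation.* The patient leaves if allocated to massage and stays if allocated to exercises. Exclusion acts on one arm only.
- *Known beforehand, and the patient placed in the exercise arm.* That patient was not allocated at random.
- *Checked in everyone beforehand, and the patient excluded whatever the arm.* This is sound, but the reference to the massage group would then have no function, and the Protocol does not describe it.

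The first two follow from the literal wording and both make the arms differ by design. The third would need the wording to change.

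**2. How often it would happen.** Inputs:

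- Total target 10, from the Sample size section.
- Massage patients n = 10 / 2 = 5. Equal allocation is an assumption; no ratio is stated.
- Allergy prevalence p. The Protocol gives none, so 0.1% to 5% is assumed.

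The chance of at least one exclusion among n massage patients is 1 − (1 − p)^n, and the expected number is n × p.

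| Assumed p | Chance of at least one, 1 − (1 − p)^5 | Expected number, 5p |
|---|---|---|
| 0.1% | 1 − 0.999^5 = 0.5% | 0.005 |
| 1% | 1 − 0.99^5 = 4.9% | 0.05 |
| 2% | 1 − 0.98^5 = 9.6% | 0.10 |
| 5% | 1 − 0.95^5 = 22.6% | 0.25 |

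**3. How far it would move the comparison.** Let D be the mean difference in outcome between allergic and non-allergic patients. If allergic patients are kept in the exercise arm and absent from the massage arm, the expected exercise mean contains a share p of them, and the difference between arms shifts by p × D. At D = 1 SD, itself an assumption, this is 0.001 × 1 = 0.001 SD at the low end and 0.05 × 1 = 0.05 SD at the high end. If D = 0, the shift is zero.

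**4. What a single case means.** With 5 per arm, one patient is 1/5 = 20% of an arm.

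**5. After the change.** If the same criterion is applied to every candidate before allocation, the differential exclusion is zero by design, and so is the p × D shift. The sample size is unaffected.

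**The case against.** The strongest reply is that the phrase is loose drafting. The item sits among baseline conditions that would ordinarily be checked at entry, and naming the massage group may only explain why olive oil matters. The document is a short registry entry, and the investigators may have meant to screen everyone. This is possible, and it is why the point is about what the criterion states and not about what was done. It does not remove the point: the restriction appears in both places, no other criterion carries one, and nothing in the Protocol describes screening for the allergy before allocation.

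The reply on size largely stands. At the assumed prevalences, the chance that no massage patient is affected is between 99.5% and 77.4% (100% minus the figures in the table). Nothing in the Protocol links olive-oil allergy to limb strength, so there is no stated reason to expect a large D.

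Three stronger inferences are tempting, and the documents do not support them.

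- *That the criterion breaks randomisation or undoes the balance on sex, age and hospital.* Harm needs an allergic patient to be enrolled and then treated differently by arm, which is unlikely on most of the assumed range.
- *That a fifth of the massage arm would be lost.* The Randomization description says that allocation goes on until the planned number is reached, so a removed patient might be replaced. Replacement would not restore comparability, but a net loss is not established.
- *That the unblinded team could use the criterion to remove patients selectively.* Allocation is done by a researcher with no part in intervention or outcome measurement. That does not cover removals afterwards, but nothing in the text suggests discretionary use.

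**Conclusion.** The point holds as a fault in a stated rule: read literally, eligibility depends on the allocated arm, in an open-label trial, so the arms need not represent the same population. It is not a matter left to an analysis plan, because the eligibility criteria are fixed in the Protocol.

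Its expected effect is small: a chance of roughly 0.5% to 23% that any massage patient is excluded in this way, and an expected shift of at most 0.05 SD even if allergic patients differ by a full SD. These figures rest on 5 massage patients and on prevalences from 0.1% to 5%, none of which the Protocol states. Bias arises only if such patients differ in prognosis. The reasons to act are that one case would weigh heavily among 10 patients and that the correction is nearly free. It is a worthwhile correction, not one on which the trial's validity turns.

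**What to change.** In both the Exclusion criteria section and the protocol summary, delete the words that tie olive-oil allergy to the massage group. State that the allergy is assessed in every candidate before allocation and excludes from both arms. The cost is one screening question for everyone and the loss of a very few patients who could have entered the exercise arm.

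The Protocol gives the recruitment status as complete, although the actual recruitment dates are blank. If recruitment has ended, a change of wording cannot alter who was enrolled. In that case, report how many patients were removed or redirected under this criterion, and whether this was before or after allocation, and keep any allocated patient in the assigned arm for analysis. This costs a check of the screening and allocation records.

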**Age**  
From **18 years** old

**Gender**  
Both

**Phase**  
N/A

**Groups that have been masked**  
*No information*

**Sample size**  
Target sample size: **10**

**Randomization (investigator's opinion)**  
Randomized

**Randomization description**  
Samples will be divided into two groups (massage group, range of motion exercises) using the minimization method. In the minimization method, sex, age ( $\pm 2$ ), and hospital are considered as matched variables at baseline. In other words, in each hospital, the first sample will be placed in one of the groups using the lottery, and the next sample will be randomly assigned to one of the groups after matching the groups by gender and age. This process will continue until the sample volume is complete. Random allocation of samples to each group will be done by a researcher who has no role in intervention and outcome measurement.

**Blinding (investigator's opinion)**  
Not blinded

**Blinding description**  
**Placebo**

Not used

**Assignment**  
Parallel

**Other design features**

**Secondary Ids**  
empty

**Ethics committees**

**1**

**Ethics committee**  
**Name of ethics committee**  
 Ethics committee of Kerman University of Medical Sciences  

**Approval date**  
 2020-01-20, 1398/10/30  
**Ethics committee reference number**  
 IR.KMU.REC.1398.558

**Health conditions studied**

**1**

**Description of health condition studied**  
Intensive Care Units Acquired Weakness

**ICD-10 code**  
**ICD-10 code description**

**Primary outcomes**

**1**

**Description**  
Change in the score of Intensive Care Units Acquired Weakness

**Timepoint**  
Before the intervention, the fourth day of the intervention, and at the end of the seventh day of the intervention

**Method of measurement**  
The Medical Research Council (MRC) physical strength examination and the Lafayette Hand-Held Dynamometer (HHD) Model (01163)

**Secondary outcomes**  
empty

## Intervention groups

### 1

#### Description

Intervention group: Massage group: Intervention in this group begins on the first day of admission. In this group, in addition to providing routine care, the researcher/fellow researcher massages the entire body once a day for 7 consecutive days using the Swedish massage style. To do the massage, first placing the mat so that the patient's mattress will not get oily and the patient is positioned. Massage is in such a way that the patient will be in the supine position and the head is positioned at an angle of 30 to 45 degrees. Swedish massage comprises strokes, gliding, and vibrating. For massage, olive oil is used to the extent that facilitates massage (approx. 20 ccs). The whole-body massage will be continuous and lasts 30-60 minutes. Massage is performed at 3 to 7 pm when the intensive care unit workload is less. After the massage is completed, the patient's entire body is cleaned with a napkin to cleanse the remaining oil on the patient's body.

#### Category

Rehabilitation

### 2

#### Description

Intervention group: Range of motion exercises group: The intervention in this group begins on the first day of admission. In this group, in addition to providing routine care, the researcher performs a passive and active range of motion exercises once a day for 7 consecutive days. The intervention is that the patient is first placed in the supine position. Passive range of motion exercises of the upper extremities include fingers, wrists, elbows, shoulders, and lower extremity passive range of motion exercises include toes, ankles, knees, thighs. All movements are performed gently and rhythmically and repeated 10 times. The range of motion exercises will take 30-60 minutes. The parameters indicating intolerance of range of motion exercises are as follows: mean arterial pressure  $\leq 65$  mmHg, systolic blood pressure  $200 \leq$  mmHg, heart rate  $\leq 40$  or  $130 \leq$ , oxygen saturation percentage  $\leq 88\%$ , respiratory rate  $\leq 5$  or  $30 \leq$  per minute, and arrhythmia. In case of intolerance, until the patient's condition is stabilized, the continuation of the range of motion exercises will be postponed. The range of motion exercises will be performed from 3 to 7 pm.

#### Category

Rehabilitation

## Sponsors / Funding sources

### 1

#### Sponsor

**Name of organization / entity**

Kerman University of Medical Sciences

**Grant name**

**Grant code / Reference number**

**Is the source of funding the same sponsor organization/entity?**

Yes

**Title of funding source**

Kerman University of Medical Sciences

**Proportion provided by this source**

100

**Public or private sector**

Public

**Domestic or foreign origin**

Domestic

**Category of foreign source of funding**

empty

**Country of origin****Type of organization providing the funding**

Academic

**Email**

[contact]

**Sharing plan****Deidentified Individual Participant Data Set (IPD)**Undecided - It is not yet known if there will be a plan to  
make this available**Study Protocol**Undecided - It is not yet known if there will be a plan to  
make this available**Statistical Analysis Plan**Undecided - It is not yet known if there will be a plan to  
make this available**Informed Consent Form**Undecided - It is not yet known if there will be a plan to  
make this available**Clinical Study Report**Undecided - It is not yet known if there will be a plan to  
make this available**Analytic Code**Undecided - It is not yet known if there will be a plan to  
make this available**Data Dictionary**Undecided - It is not yet known if there will be a plan to  
make this available
